### Withdrawal and dropout

2.10

If participants do not meet the inclusion or exclusion criteria (for screening only), withdraw their consent, or if the participant's continued participation is judged to be inappropriate, participants will be excluded from the study. In addition, participants may be excluded from the study if there is a major violation of the human application test protocol or non-observation. Those who have taken or need to take medicines or health functional foods that may affect this clinical trial may be excluded from the study; if a participant becomes pregnant during the human application test period, the participant may be withdrawn. The researcher will record the reason for the treatment interruption and whether each participant completed the study.

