### Intervention

2.6

All eligible participants will receive treatment according to their allocated group (LP or placebo) during the 4-week treatment period. To maintain the double-blinded nature of the study, the 1000 mg LP and placebo will be manufactured to be indistinguishable in appearance by D&L Biochem (Chungju, Republic of Korea). One capsule will be taken orally twice a day. Any other treatment received during their participation in the trial, functional health foods taken, or additional therapies will be considered to be combination therapy. If coadministration is necessary, the administration details will be recorded in the case report form and treatment chart, and the existing therapy will remain unchanged. The participants will be evaluated after 4 weeks.

Concomitant drug administration will however be minimized during trial participation, and will be allowed based on the judgment of the principal investigator when it is deemed inconsequential to the trial. If a drug directly affects immune function, that participant will be withdrawn from the trial.

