### Outcome measures

2.7

The primary outcome is the BCSS score, which will be used to assess respiratory symptoms, such as dyspnea, cough, and sputum. The secondary outcomes are the pulmonary function test (FVC, FEV1, FEV1/FVC), the clinical symptoms of cough and sputum (assessed through a questionnaire), high-sensitivity C-reactive protein level, erythrocyte sedimentation rate, white blood cell count, eosinophil, T cell, B cell, and immune factors (interleukin (IL)-1β, IL-4, tumor necrosis factor (TNF)-α, IL-6, IL-8, interferon (IFN)-γ, immunoglobulin (Ig)E) to analyze allergic inflammation in the bronchi, antioxidants (glutathione peroxidase, superoxide dismutase, nitric oxide) to analyze bronchial peroxide expression levels, and COPD assessment test score. All outcome measures will be assessed at the first and second visits. To ensure the safety of the participant, we will conduct laboratory tests, such as liver function, complete blood count, and electrolytes, and evaluate vital signs at every visit. Safety assessments will be conducted during the second visit. The participants’ data will be anonymized and coded using a specific program (Fig. 2).

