### Statistical analysis

2.9

Statistical analyses will be performed using the principle of the full analysis set (FAS). For the intention-to-treat analysis, missing values will be analyzed as last observation carried forward. The baseline values before treatment and the changes in BCSS scores after 4 weeks of treatment will be measured for the experimental and control groups. To test the mean rank sum of BCSS changes after the 4 weeks compared to baseline between the 2 groups, the Mann–Whitney-Wilcoxon rank sum test will be performed. The treatment difference between the treatment and control groups will be estimated using the Hodges-Lehmann method, and a 95% nonparametric confidence interval will be presented. The confidence level will be set to 5%. All statistical analyses will be performed using SPSS Statistics for Windows version 21.0 (IBM Corp., Armonk, NY).

Descriptive statistics, such as the number of participants, and the mean, standard deviation, minimum, median, and maximum of data, will be presented for each visit, as well as changes from baseline at the final evaluation for continuous data, clinical laboratory tests, and vital signs. No intermediate analyses will be performed.

Descriptive statistics for demographic data and clinical history data for the FAS group will be presented. Continuous data will be tested using *t*-tests or Wilcoxon's rank sum tests. Categorical data will be analyzed using the chi-square test or Fisher exact test.

The safety assessment calculates the rate of adverse events. Continuous data such as comparisons between groups, individual laboratory test results, and biomarkers will be analyzed using paired *t*-tests or *t*-tests with 95% confidence intervals within the group to determine if there are any changes compared to the baseline. If the assumption of normality is not met, nonparametric statistical analyses (Wilcoxon signed rank test or Wilcoxon rank sum test) will be performed. Categorical data will provide frequencies and ratios for each category. The differences between groups will be analyzed using the chi-square test and Fisher's exact test.

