### Safety

2.11

The occurrence of side effects will be assessed at each visit. Subjects will be monitored for undesirable and unintended symptoms, signs, and diseases. All adverse events will be classified and evaluated as mild, moderate, or severe. If a serious adverse event occurs, it will be reported to the IRB within 24 hours of identification and the participant will be required to withdraw. The number and ratio of participants who experience adverse events will be recorded.

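### Withdrawal rules take randomised participants out of the study, not only off the product, so their Week 4 BCSS can be lost or set aside despite the FAS/ITT principle

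*Protocol article*

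**What the plan says.** **Removal from the study (section 2.10).** Failing the eligibility criteria counts at screening only, so the other grounds reach randomised participants.
- Two grounds are discretionary: "participants may be excluded from the study if there is a major violation of the human application test protocol or non-observation", and "Those who have taken or need to take medicines or health functional foods that may affect this clinical trial may be excluded from the study". Pregnancy is also worded as a possibility.
- A third ground is open-ended: anyone whose continued participation is judged inappropriate is to be excluded.

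**Concomitant treatment (section 2.6).** "If coadministration is necessary, the administration details will be recorded in the case report form and treatment chart", with existing therapy left as it is. The next paragraph lets the principal investigator allow drugs that do not matter for the trial. A drug acting directly on immune function leads to withdrawal from the trial.

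**Serious adverse events (section 2.11).** After such an event "the participant will be required to withdraw". The sentence does not say whether from the product or from the trial. Beside sections 2.6 and 2.10, leaving the trial is the natural reading.

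**Assessments (section 2.7).** "All outcome measures will be assessed at the first and second visits". There is one post-baseline BCSS, at Week 4.

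**Analysis (section 2.9).** The full analysis set is the governing principle, and "For the intention-to-treat analysis, missing values will be analyzed as last observation carried forward". The primary comparison is a rank sum test on BCSS change, with a Hodges-Lehmann estimate and a 95% confidence interval.

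**The concern.** An analysis of all randomised participants needs their outcomes. The removal rules mix two different events, stopping the product and leaving the study, and the article nowhere keeps the Week 4 assessment for someone who is removed.

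Some triggers can be related to the primary outcome. Participants enter with cough and sputum, and BCSS scores breathlessness, cough and sputum. A participant whose symptoms worsen is one who may come to need a medicine that could affect the trial. If that person is removed, a poor outcome is replaced by no change or disappears. With 11 per arm, a few such cases can move the estimate. The trial is meant to inform later sample sizes (section 2.4), so a distorted estimate would be carried forward.

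**Working it through.** **1. Which rules reach randomised participants**

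| Ground | Section | Force | Can relate to symptoms? |
|---|---|---|---|
| Major violation, non-observation | 2.10 | discretionary | possibly |
| Other medicines or functional foods | 2.10 | discretionary | yes, if needed for worsening |
| Participation judged inappropriate | 2.10 | mandatory once judged | possibly |
| Immune-active drug | 2.6 | mandatory | possibly |
| Serious adverse event | 2.11 | mandatory | possibly |
| Pregnancy | 2.10 | discretionary | no |

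**2. What happens to the outcome**

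Table 1 has efficacy measurements at Visits 1 and 2 only, with no visit between. That leaves two routes.
- *Removed before Visit 2.* The last observation is the baseline. LOCF gives change = baseline − baseline = 0. If the analysis set requires a post-baseline value, the person drops out instead.
- *Excluded at Visit 2.* Compliance and concomitant drugs are checked at that visit, and withdrawal criteria are confirmed there too. BCSS is measured at the same visit, so a value can exist, but exclusion from the study could set it aside.

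**3. The plan's own figure**

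Section 2.4 gives 10 per group and 5% dropout. 10/0.95 = 10.53, rounded up to 11 per group, so 22 in total; this reproduces. Expected losses are 0.05 × 22 = 1.1. The binomial probability of losing 3 or more of 22 is 0.095 at 5%, 0.38 at 10%, 0.66 at 15% and 0.85 at 20%. Only 5% is the plan's rate; the others are a range.

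**4. Illustration with the planned estimator**

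Assumptions, none from the protocol: normal changes, SD 1, 11 per arm, no true effect, and the worst k placebo participants removed. The mean change in both arms is 0 or −0.5 SD (negative is improvement). There were 2,000 simulated trials per scenario. Entries are the mean Hodges-Lehmann estimate, LP minus placebo, in SD; positive is against LP. The two-sided 5% rejection rate is in brackets.

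| Mean change | k | LOCF (change = 0) | Dropped |
|---|---|---|---|
| 0 | 1 | 0.116 (0.070) | 0.131 (0.060) |
| 0 | 2 | 0.205 (0.091) | 0.287 (0.106) |
| 0 | 3 | 0.276 (0.134) | 0.409 (0.155) |
| −0.5 | 1 | 0.073 (0.061) | 0.128 (0.060) |
| −0.5 | 2 | 0.104 (0.058) | 0.270 (0.106) |
| −0.5 | 3 | 0.125 (0.040) | 0.392 (0.146) |

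With complete data and no effect, the same code gave estimates within about 0.02 of zero and rejection rates of 0.036 to 0.059. The lower bracketed rates are therefore within simulation noise. With an assumed true benefit of 0.5 SD, the estimated benefit fell to between 0.43 and 0.22 SD (LOCF) and between 0.37 and 0.11 SD (dropped).

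Removing the worst LP participants instead would mirror the null shifts in LP's favour. Removing the worst two on placebo and the worst one on LP left 0.04 to 0.09 SD (LOCF) and 0.11 to 0.14 SD (dropped). With no true effect, equal removal in both arms gives zero expected shift by symmetry.

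**5. Hand check on the mean**

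The expected two largest of 11 standard normals are 1.586 and 1.062, sum 2.648. With mean change 0, LOCF moves the arm mean by 1.586/11 = 0.144 and 2.648/11 = 0.241 SD. Deletion moves it by 1.586/10 = 0.159 and 2.648/9 = 0.294 SD. The simulated shifts are of the same order and somewhat smaller.

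**The case against.** Several points on the other side stand and set the limits of the finding.

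- **A reader might infer that Week 4 data are never collected for anyone who is removed.** The article does not say so. Table 1 places the compliance and medication checks at the visit where BCSS is measured, so many cases would come to light with a value in hand. Absence of a post-baseline value follows only for removal before Visit 2. The full protocol may also contain an early-termination assessment.
- **A reader might infer that all removals are discretionary.** Those for a serious adverse event and for immune-active drugs are mandatory. The discretion lies in section 2.10.
- **A reader might infer that sections 2.6 and 2.10 give opposite rules for the same people.** Section 2.6 allows drugs judged not to matter, while section 2.10 concerns those that may affect the trial. These are largely different classes. The boundary is loose and left to judgement, so the wording needs reconciling, but a flat contradiction is not shown.
- **A reader might take the shifts as expected bias, or as a fraction of the moderate effect in section 2.4.** They are a selective case in which exactly the worst participants of one arm are lost. Participants, researchers and assessors are blinded (section 2.5), which limits removal driven by allocation. The article gives no number for a moderate effect, so no percentage of it can be stated.

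The trial is also a pilot with one short treatment interval. None of this removes the core. Blinding does not prevent removal driven by symptoms, and LOCF from baseline keeps the participant in the count without recovering the outcome.

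**Conclusion.** The point holds in limited form and should be corrected. As written, the rules take randomised participants out of the study for post-randomisation reasons, some of which can be related to BCSS, and nothing in the article protects their Week 4 value. It is either absent and imputed as no change, or at risk of being set aside, and both undercut the FAS/ITT principle.

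The size is not known. Under the stated assumptions, with no true effect and 1 to 3 of 11 removed from one arm, the shift is about 0.07 to 0.28 SD under LOCF and 0.13 to 0.41 SD if they are dropped. The sign depends on which arm loses people. The conclusion rests on reading exclusion from the study as ending follow-up or use of the data. A provision in the full protocol that keeps Visit 2 and its data would answer it.

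**What to change.** 1. In sections 2.6, 2.10 and 2.11, separate stopping the product from leaving the study. The clinical grounds for stopping are not in question and stay as they are.
2. State that every randomised participant who has not withdrawn consent attends Visit 2 for BCSS and safety, whatever the violations, other medicines or product discontinuation, and is analysed in the assigned arm.
3. Use violations and other medicines only to define a supportive per-protocol set, fixed before unblinding.
4. Reconcile the wording on concomitant medicines in section 2.6 with that in section 2.10.

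The cost is a short amendment. Visit 2 is already scheduled for everyone, so no visit or procedure is added.

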### Safety

2.11

The occurrence of side effects will be assessed at each visit. Subjects will be monitored for undesirable and unintended symptoms, signs, and diseases. All adverse events will be classified and evaluated as mild, moderate, or severe. If a serious adverse event occurs, it will be reported to the IRB within 24 hours of identification and the participant will be required to withdraw. The number and ratio of participants who experience adverse events will be recorded.

### Ethics

2.12

The study design is in accordance with the Helsinki Declaration and the Korean Clinical Practice Guidelines and was approved by the Korean IRB of DUCKMH (approval number DJUMC-2021-BM-02-1). This study protocol was registered with the Korean National Clinical Research Information Service (CRIS) (CRIS-KCT0006426). Any participant in this study may withdraw consent or voluntarily cease to participate at any time for any reason.

## Discussion

3

The lungs and respiratory system prevent various diseases by activating the immune system when viruses invade.^[11]^ However, because they are connected to the outside environment, inflammation occurs easily, leading to symptoms.^[12]^ The most common symptoms are cough, sputum, and shortness of breath; exposure to external fine dust, viruses, and other air pollutants is considered a risk factor.^[4]^

Respiratory diseases such as bronchitis, asthma, and COPD are among the most common diseases, and respiratory symptoms are closely related to discomfort in daily life.^[3]^ Therefore, interest in easily accessible health functional products and complementary medicine has increased. Studies are being actively conducted to discover immune-enhancing substances or extracts isolated from natural herbal supplements.^[13]^

As a traditional Asian herbal medicine, LP has long been used for the treatment of asthma, as well as bronchial and lung inflammation,^[14,15]^ and it is said to act as a defense mechanism against fine dust and respiratory diseases.^[16]^

There have been previous studies on the actions and effects of LP. Kim et al reported that LP generated an immunomodulatory effect through T cells and the promotion of INF-γ secretion.^[17]^ Ryu et al reported the effects of LP on the secretion of cytokines, eosinophils, and IgE in relation to asthma.^[16,18]^ Kim et al reported the effects of LP on immune cells in a rat asthma model.^[19]^ LP has also been shown to potently inhibit airway inflammation and hyperresponsiveness in a murine model of asthma by modulating the relationship between Th1/Th2 cytokine imbalance.^[20]^ Most recently, LP has been noted to suppress the increased inflammatory cytokines in lung phagocytic cells or epithelial cells caused by fine dust in a dose-dependent manner.^[5,21]^

The proposed study will be the first at this stage to be conducted to determine the appropriate dosage and duration of LP administration. Although our sample size will be small and biases may result, this study will provide valuable insights into the underlying mechanisms of the anti-inflammatory effects and improvement of respiratory function caused by LP extract and will lay the groundwork for further studies.
